### Intervention

In both conditions, the participating children will attend 20 sessions of Taekwondo training. Except for the experimental manipulation (the presence or absence of music), children will receive the same level, skills, and duration of Taekwondo training across both conditions. The training will be administered in a group setting (six children per class), twice a week over 10 consecutive weeks. Each training session will last for 45 minutes and consist of warming-up exercises, hand movements, stance, foot movement techniques, a combination of stance and hand and foot techniques, and cool-down exercises. The teaching syllabus will follow the white belt (most junior) rank of the Taekwondo grading system. A qualified Taekwondo coach will conduct the training alongside a teaching assistant and two student assistants in each session.

In the Taekwondo training with elements of music therapy group, elements of music therapy will be incorporated into exercise training. Each piece of music will be tailor-made according to the rhythm, dynamic, tempo, duration, and associated feeling of a series of Taekwondo movements. For example, when forceful kicking is necessary, music with a rapid rhythm and strong, heavily accented beat will be applied. The music will serve to guide the motor patterns in a feedforward manner. The coaches will provide demonstrations that follow the tempo and rhythm of the specially composed music to guide the children in completing the Taekwondo movements. Short songs will also be composed, recorded, and played to accompany recurrent activities such as deep breathing and movement transitions. These short music pieces will offer cues to the children for recurrent activities and increase their success in effectively following the coach’s lead.

Teaching assistants will document attendance rate and any significant events during the study period. Participants who have been consistently absent will be contacted to investigate the reasons for their absence and to encourage regular attendance. If a participant drops out of the training sessions, they will still be invited to complete the post-training and 2-month follow-up assessments. All kinds of ASD-related concomitant trainings are permitted during the study period and information on these trainings will be recorded.

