#### 1. Immediate effects in the training sessions

*1*.*1 Engagement in the training sessions (primary outcome)*. Training sessions will be videotaped and coded. The direct observation component of the Revised Individual Child Engagement Record (ICER-R) system will be applied to record individual children’s engagement [35,36] during the training sessions. The ICER-R uses a 15-second momentary time sampling approach and involves the coding of types of engagement, the occurrence of interaction with partners (coach or peers), and whether the child was physically prompted. The types of engagement being coded at each 15-second interval are active engagement, passive engagement, active non-engagement, and passive non-engagement. Anecdotal information including emotional response was recorded during the observation for qualitative analysis. The mean inter-observer agreement is 83% for engagement, 88.7% for interaction occurrence, and 96.8% for interaction partner [35]. The engagement during the training session is expected to be the most sensitive to changes induced by music therapy, as the music is specifically designed to match the rhythm and dynamics of the Taekwondo movements. This is supported by two previous studies showing that incorporating musical elements into exercise training/activities significantly increased the engagement level in children with autism [18,26].

*1*.*2 Enjoyment state*. The Children’s Emotional Manifestation Scale (CEMS) will be used to assess the children’s emotional state at the end of each training session. Children will be asked to select which cartoon facial expression most represents their emotional state. The numbers obtained for each category are added together to obtain the total score. High scores indicate the manifestation of more negative emotional behavior. The interrater reliability coefficient of the CEMS is 0.96, and its internal consistency has an alpha coefficient of 0.92 [37].

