### Sample size calculation

A previous study that used jogging as an exercise format in a group of children with ASD aged 5 to 13 years demonstrated that the percentage of time the participants spent in vigorous exercise, which correlates with engagement, was significantly higher under the slow-music condition (a tempo of 60, which is similar to the songs developed in this proposal) compared with the non-music condition (mean difference = 11.8%, common SD = 21.6%, effect size d = 0.55) [26]. Another study also revealed that music increased the engagement of students with autism during group activities [18], as the percentage of time in class during which participants exhibited active engagement behaviors increased from 44.7% ± 16.9% to 68.8% ± 13% (effect size d = 1.61). Considering these studies, assuming an effect size (d) of at least 0.55 in the primary outcome proposed for this study (engagement) will be observed for the Taekwondo training with elements of music therapy condition in contrast to the Taekwondo training alone condition, a minimum of 54 subjects are required to detect such an effect with a power of 80% and type I error of 0.05. To account for a 20% attrition rate and the requirement of pairing-up children for practice per group, 72 participants will be recruited in total.

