### Statistical analysis

The participants’ characteristics and primary and secondary outcomes will be evaluated using summary statistics, including mean (SD), median (IQR), or proportions as appropriate, at multiple time points. The primary analysis will consist of an intention-to-treat analysis comparing the primary outcome (engagement) between the two intervention groups; specifically, a linear mixed-effect model will be used to investigate the effect of intervention (Taekwondo training with vs without elements of music therapy) over time (interaction between intervention and time) on the engagement in the training sessions, with a random effect for each participant. The effects of music therapy on the secondary outcomes measured during the training sessions, including physical activity levels, enjoyment state, and the rate of perceived exertion, will be tested by independent samples t-tests. Further, we will use a linear regression model to investigate the effect of intervention on these outcomes, adjusting for the following prognostic variables: age, sex, and BMI. A log transformation will be applied for any outcomes resulting in a skewed distribution.

For the other secondary outcomes measured before and after the training sessions, a linear mixed-effect model will be used to investigate the effect of intervention over time (interaction between intervention and time), with a random effect for each participantand adjusting for the following prognostic variables: age, sex, and BMI. The analyses will also evaluate the sustained benefits of the training by assessing the effect of the intervention on the secondary outcomes at the 2-month follow-up using the statistical methods described above. The significance level will be set at *p*< .05, and all analyses will be performed using SPSS (v25.0 for Windows; IBM, Armonk, NY, USA).

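### The primary mixed model has one random effect per child, so an intervention-by-time test fitted as a linear trend over many sessions is anti-conservative if children's engagement trends differ

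*Protocol article*

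**What the plan says.** The Statistical analysis section of the protocol article names three things for the primary outcome: the model (linear mixed-effect, intention to treat), the tested term and the random part. The effect of intervention is examined "over time (interaction between intervention and time) on the engagement in the training sessions, with a random effect for each participant". No random slope, residual correlation structure or robust standard error is mentioned.

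The outcome is measured repeatedly. Under Intervention, "the participating children will attend 20 sessions of Taekwondo training". Under Immediate effects in the training sessions, "Training sessions will be videotaped and coded". The article does not say how many sessions are coded for the primary analysis, or whether time is a linear trend or a set of categories. The significance level is 0.05; two-sided testing is assumed here.

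**The concern.** An intervention-by-time interaction compares change between arms. The error term for such a comparison must reflect how much change varies from child to child, because children are the randomised units. A random intercept removes only differences in level. If children's trends differ, that variation goes into the residual, where the model counts it as noise independent between sessions and averages it over all sessions. In truth it averages only over children.

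Differing trends are plausible in this trial. The Abstract builds its rationale on unequal response between children in earlier exercise programmes and offers poor engagement as one explanation. The Introduction lists inattention and difficulty in regulating emotion among the obstacles to teaching. None of this measures the spread of engagement trends, but one common trend per arm is a strong assumption beside it.

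At stake is the error rate of the trial's only primary test. The coders of the video outcome are not blinded, so a significant result will be examined closely in any case.

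**Working it through.** The plan has no figure for this point beyond the nominal 5%. Its sample size rests on a difference in means ("mean difference = 11.8%, common SD = 21.6%, effect size d = 0.55"; 11.8/21.6 = 0.546), not on a slope, and is not used below.

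**Inputs.** From the protocol: at most 20 sessions, 1:1 allocation, alpha 0.05. Assumed, because the protocol gives none: residual SD s_e of 10, 15 or 20 percentage points; between-child slope SD s_b of 0.3, 0.5 or 0.7 points per session, which is 5.7, 9.5 or 13.3 points from session 1 to session 20 (times 19); time linear; coded sessions equally spaced over the programme.

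**Formulas** for m coded sessions, with Sxx the sum of squared deviations of session number from its mean:

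- True variance of one child's fitted slope: V_true = s_e²/Sxx + s_b²
- Variance assumed by the random-intercept model: V_model = (s_e² + s_b²·Sxx/(m−1))/Sxx
- k = √(V_true/V_model); type I error = 2·(1 − Φ(1.96/k))

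The number of children cancels from k, so a larger sample does not cure the problem.

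**Worked example**, m = 20, Sxx = 665, s_e = 15, s_b = 0.5. V_true = 225/665 + 0.25 = 0.588. V_model = (225 + 0.25 × 665/19)/665 = 233.75/665 = 0.3515. k = √1.674 = 1.294. 1.96/1.294 = 1.515, which gives 13.0%.

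**Grid**, type I error in % for s_b = 0.3 / 0.5 / 0.7:

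| Coded sessions (Sxx) | s_e = 10 | s_e = 15 | s_e = 20 |
|---|---|---|---|
| 20 (665) | 11.5 / 21.0 / 30.4 | 7.9 / 13.0 / 19.4 | 6.6 / 9.6 / 13.7 |
| 10 (367.7) | 8.4 / 13.7 / 20.0 | 6.5 / 9.1 / 12.7 | 5.8 / 7.3 / 9.5 |
| 5 (225.6) | 6.7 / 9.4 / 12.7 | 5.8 / 7.1 / 8.9 | 5.4 / 6.2 / 7.3 |
| 4 (200.6) | 6.3 / 8.4 / 10.9 | 5.6 / 6.6 / 8.0 | 5.3 / 5.9 / 6.8 |

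**Simulation under the null**, random intercept only:

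- *Linear time.* With 36 per arm and 20 sessions, and the trend SD over the programme expressed in residual SDs, the type I error was 0.08, 0.22, 0.35 and 0.41 at trend SDs of 0.5, 1, 1.5 and 2. The closed form gives 0.10, 0.22, 0.34 and 0.43. With no trend variation it was nominal (0.05).
- *Categorical time, omnibus interaction test.* On the grid's own SDs with 20 sessions it was about 4.5 to 7%. It reached 10% only at a trend SD of 2 residual SDs, which is outside the grid (the grid's largest is 13.3/10 = 1.33).
- *Child-specific slopes* (t-test on per-child slopes): 0.036 to 0.065 in every setting.
- *Comparison of child means:* 0.037 to 0.057.

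**The case against.** The strongest objection is that the inflation needs conditions the protocol does not state.

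- **Time coding.** Linear time is nowhere specified. The same section uses the same interaction wording for secondary outcomes measured at three visits, where categorical time is the natural choice. Under categorical time with an omnibus test, the inflation all but disappears. This stands.
- **Number of sessions.** Twenty sessions are held, but the article does not say that all of them enter the model. With few coded sessions the inflation is modest even for linear time. This stands too.
- **Slope variation.** All the SDs are assumptions. The Abstract's remark on unequal improvement concerns earlier programmes, not session-to-session engagement. It makes differing trends plausible but gives no size.
- **Level of detail.** Covariance structures, degrees of freedom and fallbacks often belong in an analysis plan, which is not shown and might add a slope. This stands only in part. The article does not leave the model open: it names the tested term and the random part, and that pairing is what is questioned.
- **Relevance.** The hypothesis and the sample size concern average engagement, and a comparison of child means holds its size. That limits the point to the interaction test, but the interaction is what the article makes primary.

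A reader might infer that the primary test will fail to hold 5%, or that its standard error is certainly too small. The documents do not support that, because the time coding, the number of coded sessions and the spread of children's trends are all unstated.

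**Conclusion.** The point holds conditionally. Read in the ordinary way, the stated random structure does not protect the stated interaction test when three things coincide: time is a linear trend, many sessions are coded, and children's trends differ. Under the assumed SDs, the type I error is then about 7 to 30% with 20 sessions, 6 to 20% with 10, and 5 to 13% with four or five. It is near nominal for an omnibus categorical-time test, nominal if trends do not differ, and unaffected if child means are compared. The ranges rest on assumed SDs, no residual correlation structure and equally spaced sessions. The change should be made before the data are analysed, since choosing the random structure afterwards would itself depend on the data.

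**What to change.** State how many sessions are coded for the primary analysis and how time is coded. Wherever a trend over sessions is tested against intervention, specify a random intercept and a random slope for session per child (unstructured 2×2 covariance) with Satterthwaite degrees of freedom, and name the fallback if the model does not converge. A comparison between arms of slopes fitted child by child would serve as that fallback, since it needs no iterative fit. It could also replace the mixed-model test outright; the two are equivalent when every child has the same coded sessions. If the primary contrast is changed to each child's mean engagement, no random slope is needed.

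The cost is a sentence or two in the analysis section and no extra data. The interaction will have a wider confidence interval, and the fallback will occasionally be used.

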*1*.*3 Physical activity level*. Participants will also wear an optical heart rate monitor (Polar OH1Electro Oy, Kempele, Finland) [38] on their forearms to measure their exercise heart rate as a reflection of their physical activity level during the training. Continuous heart rate data will be recorded for every session and expressed as the mean heart rate per minute. The measured exercise heart rate greater than 55% and less than 70% of each individual’s maximum heart rate (estimated as 220 minus age) will be used as individualized cutoffs for moderate- and vigorous-intensity cardiovascular workload, respectively [39].

*1*.*4 Rate of perceived exertion (RPE)*. Children will be asked to rate their exertion level at regular time points at each training session using the Borg 6-to-20 Scale, in which “6” indicates “no exertion at all” and “20” indicates “maximal exertion” [40]. High test-retest reliability (r = 0.89) was found for Chinese-translated versions of the Borg 6–20 Rating of Perceived Exertion (RPE) scale, and the perceived efforts in the RPE were shown to be significantly correlated with heart rate, power output, and oxygen consumption in children (p<0.01) [34].

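### Heart rate, enjoyment and exertion are recorded in every session on children taught in classes, but are assigned t-tests and ordinary regression with no stated unit of analysis and no class term

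*Protocol article*

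**What the plan says.** All references are to the protocol article.

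- **Data collection** (Immediate effects in the training sessions, items 1.2 to 1.4). Enjoyment, on the Children's Emotional Manifestation Scale (CEMS), is the child's "emotional state at the end of each training session". For physical activity, "Continuous heart rate data will be recorded for every session and expressed as the mean heart rate per minute". For perceived exertion (RPE), "Children will be asked to rate their exertion level at regular time points at each training session".
- **Number of sessions and classes** (Intervention). In both arms "the participating children will attend 20 sessions of Taekwondo training", taught in classes of six.
- **Analysis of these three outcomes** (Statistical analysis). The in-session secondary outcomes, "including physical activity levels, enjoyment state, and the rate of perceived exertion, will be tested by independent samples t-tests". Next, "we will use a linear regression model to investigate the effect of intervention on these outcomes", with age, sex and BMI as covariates. No random effect is given, and nothing says how up to 20 sessions become one value per child.
- **Analysis of engagement, the primary in-session outcome** (same section). A linear mixed model is used to study the intervention-by-time interaction "on the engagement in the training sessions, with a random effect for each participant". The outcomes assessed before and after the programme also get a mixed model with a participant random effect.

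**The concern.** An independent-samples t-test and an ordinary regression both assume that every value entered is independent of the others. These data depart from that in two ways. The same child is measured in up to 20 sessions, and six children share a class, its staff and its sessions. The protocol allows for within-child dependence when it analyses engagement, but gives no reason for handling three other in-session outcomes differently.

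If the dependence is ignored, standard errors are too small and a difference between arms is declared too often. Enjoyment is named in the trial's first objective, and higher physical activity and lower exertion are among the predicted immediate effects, so these results will be read as evidence on how the music works.

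**Working it through.** The protocol gives no numerical figure for these three outcomes, so there is none to reproduce. The check asks what true type I error a nominal two-sided 5% test would have under each way of carrying out the stated method.

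**Inputs from the document**
- 36 children per arm (Randomization and blinding).
- Six children per class (Intervention), so 36 / 6 = 6 classes per arm and 12 in all.
- 20 sessions per child (Intervention), so 36 × 20 = 720 session rows per arm at full attendance.
- Significance level 0.05 (Statistical analysis); two-sided is assumed.

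**Inputs that are assumptions** (the document gives neither)
- Correlation between sessions within a child: 0.1 to 0.7.
- Intraclass correlation (ICC) between children of one class: 0.01 to 0.20.

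**Formulas**
- Design effect DE = 1 + (m − 1) × correlation, where m is the number of values sharing the dependence.
- True type I error = 2 × [1 − Φ(1.96 / √DE)].

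**Reading A: session rows entered as independent values, no class effect (m = 20)**

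| Within-child correlation | DE | True type I error | Simulated |
|---|---|---|---|
| 0.1 | 1 + 19 × 0.1 = 2.9 | 25.0% | 24.7% |
| 0.3 | 1 + 19 × 0.3 = 6.7 | 44.9% | 46.4% |
| 0.5 | 1 + 19 × 0.5 = 10.5 | 54.5% | 54.2% |
| 0.7 | 1 + 19 × 0.7 = 14.3 | 60.4% | 60.6% |

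At a correlation of 0.5, the 720 rows per arm carry the information of 720 / 10.5 ≈ 69 independent values. RPE has several readings per session, so m would be larger still if every reading were a row.

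**Reading B: one mean per child, no class effect**

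The simulated type I error is 4.8% to 5.0%. Averaging removes the inflation from the repeats.

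**Reading C: one mean per child, class effect present but ignored (m = 6)**

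| Class ICC of the child means | DE | True type I error |
|---|---|---|
| 0.01 | 1 + 5 × 0.01 = 1.05 | 5.6% |
| 0.02 | 1.10 | 6.2% |
| 0.05 | 1.25 | 8.0% |
| 0.10 | 1.50 | 11.0% |
| 0.20 | 2.00 | 16.6% |

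Simulation gave 7.1%, 10.9% and 16.1% at class ICCs of about 0.04, 0.095 and 0.19, in line with the formula.

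**Comparison: a test that respects class**

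A t-test on class means (6 against 6) held 4.9% to 5.5% in every simulated setting.

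The simulations used 2 arms × 6 classes × 6 children × 20 sessions with no true effect (20,000 runs; 4,000 for the session-row test).

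**The case against.** The strongest reply is that the protocol never says session rows will be entered as separate observations. A t-test between two randomised groups of 36 children can be read just as naturally as one summary value per child, which is a standard and valid way to handle repeats, and a journal article may leave the averaging step to a fuller document. This stands. A reader might infer that the plan carries a 25% to 55% false-positive rate; the document does not support that, because those figures apply only if rows are analysed. What does not follow is that the method is then sound. The wording about mean heart rate per minute describes how a continuous recording is expressed, not averaging over 20 sessions, and nothing comparable is said for CEMS or RPE. Averaging per child also leaves class unaddressed.

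A second reply is that class is not specific to these outcomes, since the engagement and pre/post models also have only a participant random effect. That is correct: the missing class term is trial-wide, and replacing a t-test with the engagement model as written would not cure it. The reply also rightly notes that the inflation is small if the class ICC is small, 5.6% to 6.2% at 0.01 to 0.02.

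Two further criticisms are tempting but weak. One is that a t-test followed by an adjusted regression invites a choice between p-values; the order and the covariates are prespecified, and this sequence is common for secondary outcomes. The other is that averaging gives poor attenders the same weight as full attenders; that concerns efficiency, not validity.

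**Conclusion.** The point holds in a limited form. The protocol names methods that assume independent values for outcomes that are repeated within children and shared within classes, and it states neither a reduction to one value per child nor a class term.

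The size depends on how the analysis is run and on correlations that the document does not give. Session rows lead to about 25%, 45% and 55% type I error at within-child correlations of 0.1, 0.3 and 0.5. Child means lead to about 6% to 17% at class ICCs of 0.01 to 0.20, and to the nominal 5% only if classes do not differ. Full attendance and six intact classes per arm are also assumed.

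A reader might infer that the trial's main result is at risk from this. It is not: all three outcomes are secondary, and engagement has its own mixed model with a participant random effect. The change is worth making because a suitable analysis costs little.

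**What to change.** In Statistical analysis, replace the t-tests and the linear regression for heart rate, CEMS and RPE with one linear mixed model per outcome, containing:

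- group and session, plus reading within session for RPE;
- the prespecified covariates age, sex and BMI;
- random intercepts for child and for class;
- small-sample degrees of freedom, since there are only about 12 classes.

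Name the group effect averaged over sessions as the single reported test for each outcome.

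This extends the engagement model and does not copy it: that model has no class term, lists no covariates and targets the intervention-by-time interaction. The missing class term should be considered for the engagement and pre/post models as well.

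The cost is revised analysis wording, a slightly more complex model and somewhat wider intervals. No new data are needed beyond a record of each child's class, and mixed models are already planned in the same software.

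A simpler alternative is a prespecified mean per child, analysed with a random effect for class and small-sample degrees of freedom. It is also valid for the repeats, but it discards change over sessions.

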*2*.*3 Flanker inhibitory control and attention task from the NIH Toolbox Cognition Battery app*. The NIH Toolbox Cognition Battery app is a set of clinically validated iPad-based assessments [43]. The Flanker inhibitory control and attention task is chosen and will be used to assess the inhibitory and attentional aspects of executive function. On each trial, participants are presented with five arrows (or fish for participants under eight years old) in a horizontal line. The task is to indicate the direction of the middle arrow. Twenty trials were presented, with the flanking arrows alternating randomly between congruence and incongruence with the middle arrow. A scoring algorithm integrates accuracy and reaction time, yielding scores from 0 to 10. Total administration time is about three minutes. Test-retest reliability of this task is 0.95 (95% CI 0.92, 0.97), and correlations for convergent validity is r = 0.48 [43,44].

*2*.*4 Comprehensive trail-making test (CTMT)*. The CTMT targets to assess visual search speed, scanning, speed of processing, mental flexibility, and executive functioning. It consists of five visual search and sequencing tasks that are heavily influenced by attention, concentration, resistance to distraction, and cognitive flexibility (or set-shifting). The child is required to connect a series of stimuli (numbers, expressed as numerals or in word form, and letters) in a specified order as fast as possible in each trial. The time scores for the five CTMT trials will be converted to standardized T-scores according to the reference tables in the testing manual, and they will be summed up to produce a global performance level score, the CTMT Composite Index (CI), which can then be converted into a percentile score according to the participant’s chronological age. Higher T score and CTMT CI correspond to better performance. The CTMT has an internal consistency reliability coefficient of 0.92, and a test-retest reliability ranging from 0.70 to 0.78 [45].

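### The log-transformation rule ignores the direction of skew, so if engagement is left-skewed it increases the skew and moves the primary effect to a ratio scale chosen from the data

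*Protocol article*

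**What the plan says.** For the primary outcome, the Statistical analysis section states that "a linear mixed-effect model will be used to investigate the effect of intervention" over time on engagement, with a random effect for each participant. The same paragraph then gives t-tests and an adjusted linear regression for the in-session secondary outcomes (physical activity level, enjoyment, perceived exertion). It closes with the rule at issue: "A log transformation will be applied for any outcomes resulting in a skewed distribution". The next paragraph covers the outcomes measured before and after the programme and does not mention a transformation.

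Engagement comes from coded video: "The types of engagement being coded at each 15-second interval are active engagement, passive engagement, active non-engagement, and passive non-engagement" (Study measures, 1.1). The Intervention section adds "Each training session will last for 45 minutes". The Sample size calculation treats engagement and its proxy as percentages of time. It cites a study of time in vigorous exercise ("mean difference = 11.8%, common SD = 21.6%, effect size d = 0.55") and a study in which active engagement "increased from 44.7% ± 16.9% to 68.8% ± 13"%. The Flanker task (Study measures, 2.3) is scored by an algorithm "yielding scores from 0 to 10".

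**The concern.** The sentence is a positive commitment. It names one remedy, for any outcome, triggered by skew in either direction. A log compresses the upper end of a scale and stretches the lower end, so it reduces right skew and increases left skew. A percentage of intervals with a mean well above 50% is pressed against its upper bound and tends to have its longer tail on the left. That is the case in which the rule could be triggered for the primary outcome and also make matters worse.

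Two further consequences follow. First, on the log scale the treatment effect is a ratio of geometric means, not a difference in percentage points. The primary test is an intervention-by-time interaction, and interactions depend on the scale: a pattern that is parallel in percentage points is not in general parallel in ratios. Letting the observed distribution decide the scale therefore lets it decide what the primary result means. Second, the log of zero is undefined, and at least one outcome has a stated range that includes zero.

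**Working it through.** **Inputs.** From the Sample size calculation: 44.7% (SD 16.9) and 68.8% (SD 13) for active engagement; difference 11.8 and SD 21.6 for vigorous exercise; planned d = 0.55. From Randomization and blinding: 36 per arm. From Study measures and Intervention: 45 x 60 / 15 = 180 intervals per session. Assumptions of mine: engagement is analysed as a percentage of intervals, it follows a beta distribution, and a further case has mean 80% and SD 15.

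**1. The plan's own effect size.** 11.8 / 21.6 = 0.546, stated as 0.55. This reproduces, and it is a ratio of percentage-point quantities, that is, an effect on the untransformed scale.

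**2. Skewness before and after the log.** For mean m and SD s as proportions, k = m(1 - m)/s² - 1, a = mk, b = (1 - m)k.
- Raw skewness = 2(b - a)√(a + b + 1) / [(a + b + 2)√(ab)].
- Skewness of the log = [ψ''(a) - ψ''(a + b)] / [ψ'(a) - ψ'(a + b)]^1.5, where ψ' and ψ'' are the trigamma and tetragamma functions.

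For 68.8% (SD 13): k = 0.688 x 0.312 / 0.0169 - 1 = 11.70, a = 8.05, b = 3.65. Raw skewness = 2(-4.40)(3.564) / (13.70 x 5.42) = -0.42.

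| Mean (SD), % | Source | a, b | Raw | After log |
|---|---|---|---|---|
| 44.7 (16.9) | cited | 3.42, 4.23 | +0.13 | -1.06 |
| 68.8 (13) | cited | 8.05, 3.65 | -0.42 | -1.07 |
| 80 (15) | assumed | 4.89, 1.22 | -0.99 | -1.81 |

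The log moves every case towards left skew, including the near-symmetric one.

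**3. How often would the rule fire?** The article gives no criterion. Taking a skewness test at 0.05 on 72 children as an assumed trigger, simulation gives about 2%, 25% and 94% of trials for the three rows.

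**4. Effect size and power if it fires.** The intervention mean is set at m + 0.55s with the same SD, so d = 0.55 on the raw scale. The log-scale d is the difference in mean logs divided by the root mean square of the two log-scale SDs. Power = Φ(d√(36/2) - 1.96), a two-sided comparison of one value per child. On the raw scale: Φ(0.55 x 4.243 - 1.96) = Φ(0.373) = 65%.

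| Control mean (SD), % | d on log scale | Power |
|---|---|---|
| 44.7 (16.9) | 0.53 | 61-62% |
| 68.8 (13) | 0.51 | 59% |
| 80 (15), assumed | 0.45 | 48% |

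The 65% is only a common baseline for comparing the scales. Whether the stated minimum of 54 follows from d = 0.55 is a separate question.

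**5. Change of scale.** At 68.8% (SD 13) the same effect reads as 0.55 x 13 = 7.15 percentage points on the raw scale and as a geometric mean ratio of about 1.11 on the log scale. At 44.7% (SD 16.9) it reads as 0.55 x 16.9 = 9.3 points or a ratio of about 1.24.

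**6. Type I error.** In null simulations with 36 per arm, applying the trigger in step 3 mechanically gave 4.5% to 5.3%. Picking the smaller of the raw and log p-values gave at most about 6.5%.

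**7. Zeros.** With 180 intervals and these beta distributions, the chance of a session with no active engagement at all is below 0.0001 at both cited means. The Flanker range includes 0, but the article reports no distribution for it.

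**The case against.** The strongest reply concerns scope. The sentence follows directly on the t-tests and regression for the in-session secondary outcomes, and the natural narrow reading limits it to heart rate, enjoyment and perceived exertion. On that reading neither engagement nor the Flanker score is touched, perceived exertion starts at 6, and heart rate cannot be zero. That reading is available, but the wording does not impose it: the rule speaks of any outcomes and closes the paragraph that opens with the primary model. If the narrow meaning is intended, the text should say so.

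The second reply is that left skew is not established. This stands. No part of the article says how engagement will be distributed. At one of the two cited values the illustration is near-symmetric, at the other the raw skew is mild, and the beta shape is an assumption. A reader might infer that the rule will worsen the primary analysis; the documents support only that it would do so if engagement is left-skewed.

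The third reply is that an exact skewness threshold, an offset for zeros and a back-transformation normally belong in the statistical analysis plan. That also stands, and their absence is not criticised here. The criticism is of what the sentence does state: a log whatever the direction of skew.

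A reader might also infer that children scoring zero would drop out of the intention-to-treat analysis. The documents do not show this. A Flanker score of 0 is possible on the scale, but nothing indicates it will occur, and an offset could be added. The rarer engagement codes could be zero in a session, but they are not named as separately analysed outcomes.

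**Conclusion.** The point holds in conditional form. As written, the rule prescribes a transformation that corrects only right skew in positive data, for skew in either direction. If engagement is left-skewed, it increases the skew (-0.42 to about -1.07 at the cited 68.8%, SD 13), lowers a true d of 0.55 to about 0.51, costs about 6 points of power (65% to 59%), and turns the primary effect from a percentage-point difference into a ratio on the strength of the observed data. At the cited 44.7% (SD 16.9) the rule would seldom be triggered.

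The harm is mainly to interpretation, with a modest loss of power. It is not a material false-positive problem, since type I error stays near 5% under a mechanical trigger. Nor does the change of scale overturn a fixed target: the planned 0.55 is a standardised effect borrowed from a different variable, and the article commits to no percentage-point difference in engagement. The figures rest on the beta shape, on one value per child rather than the full repeated-measures model, and on engagement being analysed as a percentage of intervals. The correction is worth making because it is small and can be made before the data are seen.

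**What to change.** Replace the sentence with text that does three things.

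1. Pre-specify the primary engagement analysis on the original percentage scale, whatever the observed distribution, with robust or bootstrap standard errors if the model residuals are clearly non-normal.
2. Restrict any log transformation to secondary outcomes that are named in advance, strictly positive and right-skewed, or to sensitivity analyses. A blanket ban is not needed, because a log can suit such outcomes.
3. Optionally, add a sensitivity analysis that models the number of active-engagement intervals out of those observed with a binomial-type mixed model. It respects the 0% and 100% bounds, but its effect is an odds ratio, so it should support the percentage-point estimate and not replace it.

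If the sentence was meant only for the in-session secondary outcomes, saying so and naming them removes the problem for engagement and the Flanker score. The cost is a wording change and slightly more analysis work; no data collection changes.
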